## 6.5 Study participants characteristics

Baseline characteristics include female age, ethnicity, education, current smoking, parity, duration and type of subfertility (anovulation, tubal factor, male factor, unexplained, other), biometrics (BMI, waist circumference, waist/hip ratio, systolic and diastolic blood pressure), partner characteristics (age, BMI, current smoker), fertility characteristics (ovulation/anovulation, PCO yes/no, sperm analysis results according to WHO standards, tubal patency), and Hunault prognostic index.

## 6.6 Efficacy parameters

### Intention-to-treat analysis

The outcomes with respect to pregnancy will be tabulated for both groups. Counts will be presented and percentages will be calculated in relation to the number of started participants. The following outcomes will be described:

- Vaginal delivery of a healthy singleton >37 weeks of gestation (primary outcome, twin or higher order births counted as failure).
- Live births irrespective of term or health status (multiples counted as 1).
- Ongoing and clinical pregnancies (multiples counted as 1)
- Fetal loss: ectopic pregnancy, miscarriage (<16 weeks), still birth (before or after 24 weeks)
- Type of pregnancies: singleton or multiple
- Mode of conception: spontaneous versus fertility treatment (OI, IUI, IVF/ICSI); number of fertility treatment cycles
- Complications related to fertility treatment
- Gestational complications
- Labor and delivery characteristics (including maternal complications)
- Neonatal outcome

### Per-protocol analysis:

The outcomes with respect to pregnancy will be tabulated for both groups. Counts will be presented and percentages will be calculated in relation to the number of started participants. The following outcomes will be described:

- Vaginal delivery of a healthy singleton >37 weeks of gestation (primary outcome, twin or higher order births counted as failure).
- Live births irrespective of term or health status (multiples counted as 1).
- Ongoing and clinical pregnancies (multiples counted as 1)
- Fetal loss: ectopic pregnancy, miscarriage (<16 weeks), still birth (before or after 24 weeks)
- Type of pregnancies: singleton or multiple
- Mode of conception: spontaneous versus fertility treatment (OI, IUI, IVF/ICSI); number of fertility treatment cycles
- Complications related to fertility treatment
- Gestational complications
- Labor and delivery characteristics (including maternal complications)
- Neonatal outcome

Differences between groups will be expressed as relative risks and 95% confidence intervals.

The primary analysis will be by intention-to-treat.

The main analysis of the primary outcome will also consist of a Kaplan-Meier analysis of time to pregnancy leading to a vaginal delivery at term for both groups. The Log-rank test will be used to determine statistical significance. In this analysis, patients will be censored at the time they discontinue or complete the study without getting pregnant.

In addition, pregnancy rates and 95% confidence intervals per group will be calculated based on the Kaplan-Meier estimates at various time points. Further analysis of delivery rates over time will be performed using Cox-regression analysis with correction for the stratification variables ovulatory status and treatment centers as well as for confounders. These analyses will also be performed for spontaneous and treatment-induced pregnancies separately. The same analysis will be performed for the secondary outcome ongoing pregnancies. This will include ongoing pregnancies, which have not yet resulted in the birth of a child. The results of these analyses will be presented in a separate manuscript.

Exploratory subgroup analyses of the primary outcome and ongoing pregnancy rates will be performed for spontaneous and treatment-induced pregnancies and for women with a BMI below 35 versus above 35, as well as for anovulatory versus ovulatory women and for women with a waist-hip ratio of above 0.8 versus below or equal to 0.8 and for women who are 36 years or older versus younger than 36 years based on tests of interaction with treatment group. The results of these analyses will be presented in a separate manuscript.

Additional analysis concerning the influence of HOMA, androgens, adipokines and cytokines on pregnancy chances and recovery of ovulations in anovulatory patients will be assessed using multivariate Cox-regression. The results of these analyses will be presented in a separate manuscript.

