**Main study parameters/endpoints:**

Primary endpoint is the birth of a healthy singleton after vaginal delivery of at least 37 weeks gestation.

Secondary outcome parameters are number of fertility treatments (OI, IUI, IVF, ICSI), quality and amount of oocytes and embryos and cryo embryos derived in an IVF or ICSI procedure, the amount of embryos per transfer, implantation rate of transferred embryos, complications of fertility treatment, clinical and ongoing pregnancy rates, perinatal outcome, complications and quality of life as well as body weight, waist circumference, behaviour influencing weight, i.e. nutritional habits and exercise pattern, smoking habits, blood pressure, glucose/insulin ratio (HOMA), hormonal profile and costs.

**DATA ANALYSIS:** Analysis will be by intention to treat. Randomisation will be stratified for the presence or absence of anovulation and per treatment center. We expect an

improvement in vaginal singleton delivery beyond 37 weeks from 45% to 60%. Anticipating drop out of 20% in the intervention arm and a 5% loss to follow up in the study, we need to include two groups of 285 women (two-sided test, alpha error .05, beta-error .20).

**STUDY DURATION:** Preparation of the study, including the training of the nurses, will take three months. Inclusion of the couples will take 24 months and the lifestyle intervention will take six months. Follow up is continued for 24 months after randomisation. Database cleaning and analysis of the study will take 6 months. Duration of the study: 57 months

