#### **6.4 Withdrawal of individual subjects**

Subjects can leave the study at any time for any reason if they wish to do so without any consequences. Patients who decide to withdraw from the study will be asked by the responsible investigator to provide information regarding the primary endpoint of the study 24 months after randomisation. Patients who drop out of the study will be treated according to the local protocols for infertility patients.

The investigator can decide to withdraw a subject from the study for medical reasons.

Women who miss two consecutive counselling sessions and who are not willing to catch up are excluded from the program.

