### **8.2 Univariate analysis and multivariate analysis**

The primary analysis will be by intention to treat.

The primary outcome will be analysed by comparing the pregnancy rates in both groups using Kaplan-Meier analysis of time to pregnancy using the Log-rank test. In this analysis, patients will be censored at the time they discontinue or complete the study without getting pregnant. In addition, pregnancy rates and 95% confidence intervals per group will be calculated based on the Kaplan-Meier estimates at various time points. Further analysis of delivery rates over time will be performed using Cox-regression analysis with correction for the stratification variables ovulatory status and treatment centers as well as for confounders. These analyses will also be performed for spontaneous and treatment-induced pregnancies separately. The same analysis will be performed for the secondary outcome ongoing pregnancies. This will include ongoing pregnancies, that have not yet resulted in the birth of a child. Exploratory subgroup analyses of the primary outcome will be performed for spontaneous and treatment-induced pregnancies and for women with a BMI below 35 versus above 35, as well as for anovulatory versus ovulatory women and for women with a waist-hip ratio of above 0.8 versus below or equal to 0.8 and for women who are 36 years or older versus younger than 36 years based on tests of interaction with treatment group.

Additional analysis concerning the influence of HOMA, androgens, adipokines and cytokines on pregnancy chances and recovery of ovulations in anovulatory patients will be assessed using multivariate Cox-regression.

Incidence of complications of treatment and during pregnancy will be compared in both groups using relative risks and 95% confidence intervals.

Quality of life will be analysed using repeated measures analysis of variance

A per protocol analysis will also be performed, in which drop out patients will be identified as non-compliant. Information on the primary outcome, i.e. lifebirth within two years after randomisation will be used whenever provided. Patients who drop out of the lifestyle intervention arm will be analysed in the “usual care” arm in this per protocol analysis.

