## 6. STATISTICAL METHODS AND REPORTING

### 6.1 Sample size

On the basis of the literature the cumulative live birth rate in a follow-up of two years of subfertility treatment will be 45% for the “usual care” group. The lifestyle intervention group is estimated to have a live birth rate of 60%. We expect an improvement of healthy singleton of more than 37 week gestation born after vaginal delivery from 45% to 60% in the intervention group. Drop-out is expected to be 20% in the intervention arm^4 and is included in the analysis of effectiveness. To prove that, we need to include two groups of 272 women to be included (alpha 0.05, power 80%). To account for 5% lost to follow up 285 women will be included per group. In total, 570 women will be included.

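### The deciding log-rank analysis censors women when they discontinue, against the plan's own intention-to-treat rule, and gives no rule for women whose pregnancy ends in a non-qualifying birth

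*Supplement*

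**What the plan says.** SAP 6.6 describes the main analysis of the primary outcome in two parts. The first is a tabulation over all started participants, with "twin or higher order births counted as failure", and group differences given as relative risks. The second is a Kaplan-Meier analysis of time to a pregnancy that leads to vaginal delivery at term, with the log-rank test assigned to determine significance. The text on the second part is printed beneath the per-protocol list, but it restates that the primary analysis is by intention to treat. Its only censoring rule is "In this analysis, patients will be censored at the time they discontinue or complete the study without getting pregnant". Section 8.2 of the latest protocol names the log-rank test for the primary outcome and has the same rule: "patients will be censored at the time they discontinue or complete the study without getting pregnant".

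Three other places bear on this rule:

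- SAP 5.1.2 analyses women who drop out in the group to which they were randomised.
- Protocol 6.4: "Patients who decide to withdraw from the study will be asked by the responsible investigator to provide information regarding the primary endpoint", at 24 months after randomisation.
- SAP 6.1 plans for an improvement in healthy term singletons "born after vaginal delivery from 45% to 60% in the intervention group". It adds "Drop-out is expected to be 20% in the intervention arm", says that this drop-out is part of the effectiveness analysis, and allows separately for 5% loss to follow-up.

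**The concern.** Censoring a woman when she discontinues assumes that, from then on, she would have done as well as the women still under observation. It also sets aside any outcome she later reports, although the protocol plans to ask for it. Drop-out is expected mainly in one arm, so any error falls mainly on that arm and passes into the comparison.

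The second difficulty is a gap. A woman who conceives and then delivers by caesarean, preterm or with twins does not have the event. She is also not a woman who finished without getting pregnant, so the censoring rule does not reach her. The analyst must choose how to treat her, and the choice changes the curves and possibly the test that decides the trial.

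**Working it through.** **1. The plan's sample size.** Inputs: 45% against 60% and 20% intervention drop-out (SAP 6.1); "two-sided test, alpha error .05, beta-error .20" (protocol summary). If drop-outs revert to the usual-care rate, the lifestyle rate is 0.8 × 60% + 0.2 × 45% = 57%. With pooled variance and a mean rate of 0.51:

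n = [1.96 √(2 × 0.51 × 0.49) + 0.8416 √(0.45 × 0.55 + 0.57 × 0.43)]² / 0.12² = (1.3856 + 0.5907)² / 0.0144 = 271.2, so 272 per arm.

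This is the stated figure. The undiluted 45% against 60% would need only 173. The trial was therefore sized on an effect that still contains the drop-outs.

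**2. Censoring at discontinuation.** Assumptions: constant hazards h = −ln(1 − p)/24 per month, and discontinuation spread evenly over months 0-6. Let a fraction d discontinue. Let hs and hd be the hazards of women who stay and women who drop out. Before month 6, the hazard that Kaplan-Meier sees is

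[(1 − d) e^(−hs·t) hs + d e^(−hd·t) (1 − t/6) hd] / [(1 − d) e^(−hs·t) + d e^(−hd·t) (1 − t/6)],

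and after month 6 it is hs. The Kaplan-Meier rate is 1 − exp(−its integral to 24 months). The true rate is (1 − d) ps + d pd, where ps and pd are the two-year success rates of the two groups.

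| Discontinue | Stay | Drop out | True rate | Kaplan-Meier | Bias (points) |
|---|---|---|---|---|---|
| 20% | 60% | 45% (plan's rates) | 57.0% | 59.6% | +2.6 |
| 20% | 60% | 30% | 54.0% | 59.4% | +5.4 |
| 20% | 60% | 60% | 60.0% | 60.0% | 0 |
| 20% | 60% | 70% | 62.0% | 60.3% | −1.7 |
| 20% | 48.75% | 30% | 45.0% | 48.3% | +3.3 |
| 20% | 51.25% | 20% | 45.0% | 50.6% | +5.6 |
| 5% | 45.8% | 30% | 45.0% | 45.7% | +0.7 |
| 5% | 46.3% | 20% | 45.0% | 46.2% | +1.2 |

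The last four rows hold the arm's true rate at 45%, which is no benefit over usual care. Their staying rates are (0.45 − d·pd)/(1 − d). Every drop-out rate other than 45% is an assumption. In usual care, with 5% loss, 45% among those who stay and 30% to 60% among those lost, the shift is at most about 0.7 points either way.

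**3. Non-qualifying births, if an analyst censored them.** The documents do not give the share of births that qualify, so it is assumed. With two-year live birth rate L and qualifying share s, the true incidence is sL, and 1 − KM is 1 − (1 − L)^s.

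- s = 65%, L = 45% and 57%: 1 − KM is 32.2% and 42.2% (difference 10.0 points); true 29.3% and 37.1% (7.8).
- s = 80%: 38.0% and 49.1% (11.1); true 36.0% and 45.6% (9.6).

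The error can also go the other way. Take primary rates of 45% and 57%, and non-qualifying births in 20% of usual-care and 10% of lifestyle women. With c1 the primary rate and c2 the non-qualifying rate, 1 − KM = 1 − (1 − c1 − c2)^(c1/(c1 + c2)). This gives 51.7% and 61.1%, a difference of 9.4 points against a true 12. If these women stay in the risk set to 24 months as failures, this bias is zero in every case.

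**The case against.** **The 20% may be the wrong fraction.** The rule most naturally refers to leaving the study. The 20% is drop-out in the intervention arm, its cited source concerns lifestyle programmes, and protocol 6.4 removes women who miss sessions from the programme, not from the study. If only the 5% lost to follow-up are censored, the bias is about 1 point and similar loss in both arms would largely cancel. This stands as a limit on the size. It does not settle the matter, because the plan uses drop-out for both events and never defines discontinuation.

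**The direction is not fixed.** A reader might infer that the rule favours the lifestyle arm. That holds only if drop-outs do worse than women who stay. The plan's own rates imply this when the programme works (45% against 60%), but not when it has no effect and drop-outs also reach 45%. The low drop-out rates in the table are illustrations without support in the documents.

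**The non-qualifying births.** A reader might infer that the survival analysis censors these women and so biases both arms. The text does not say that; it gives them no rule. Carrying over the failure status used in the tabulation would leave no bias. What stands is the missing instruction.

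**The tabulation.** The relative risks over all started participants do not depend on the censoring rule, so an unaffected comparison of the same outcome is planned. This is real mitigation, but significance is assigned to the log-rank test, and the Cox model is built on the same time-to-event data.

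**Conclusion.** The point holds as a conflict and a gap within the plan. Censoring at discontinuation is an explicit instruction in the analysis that decides significance. It contradicts the intention-to-treat rule, the planned collection of outcomes after withdrawal, and the effect on which the trial was sized.

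The size depends on who counts as discontinuing and on their prognosis. It is 2.6 points in the lifestyle arm on the plan's rates if all 20% are censored over months 0-6. It is 3.3 to 5.6 points if that arm's true rate is 45% and drop-outs reach only 20-30%. It is zero with equal prognosis, negative with better prognosis, and about 1 point if only 5% are censored. Usual care is little affected.

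For non-qualifying births the defect is lack of specification. Bias arises only if they are censored, and it could enlarge or reduce the difference between arms. The documents do not support the statement that both arms' rates are biased. The stated sample size is not in error.

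**What to change.** In SAP 6.6 and protocol 8.2, delete the reference to the time of discontinuation and state:

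- Every woman is followed and analysed in her randomised arm to 24 months, whether or not she leaves the programme or stops study visits. Outcome data obtained after discontinuation are used.
- Censoring occurs only at true loss of contact, refusal of outcome data, or 24 months.
- A woman with a non-qualifying delivery counts as a failure and stays in the risk set to 24 months, for both the log-rank test and the curves. Equivalently, her outcome is a competing event in a cumulative incidence estimate with a matching test.
- Event and competing event are timed on the same clock, the date of the pregnancy, because the planned event is timed at pregnancy and not at delivery.

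The cost is a change of wording and standard software. It uses outcomes the protocol already seeks and needs no change to the sample size. With complete outcome data, the planned 45% against 57% is recovered, with 80.1% power at 272 per arm for the comparison of two proportions. The wording should be settled before database lock.

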**Nature and extent of the burden and risks associated with participation, benefit and group relatedness:**

The advantages of a weight loss and exercise program in overweight or obese subfertile women have been shown in small intervention studies. Even if the patient does not conceive during the 6 months period in the lifestyle intervention arm, the health benefits of weight loss on the long-term are clearly in the interest of the patient.

By starting this project, fertility treatment in the intervention arm will be delayed for a maximum of 6 months, there is no evidence that this delay will cause lower spontaneous or treatment dependent pregnancy chances. A more structured weight loss and exercise program will probably lead to higher spontaneous and therapy induced ongoing pregnancy chances.

**The Burden:** Patients that are randomized in the intervention arm will attend the clinic for six extra visits in order to improve lifestyle, this will take around 280 minutes. In between visits counselling will take place per telephone or mail four times for 15 minutes. During these visits physical examination, measuring weight, WC and WHR in week: one, three, seven, twelve, eighteen and twenty-four will take place. Patients in the intervention group will have to adapt their lifestyle towards a more healthy lifestyle, this will give a certain amount of stress since they will have to adapt their diet and physical activity. Patients will be learned how to use stepcounter PAM and wear it on a daily basis in order to monitor their physical activity during the intervention period and will fill in their activity list.

Patients who have been randomized in the “usual care” group will undergo fertility treatment when indicated by national guidelines ([www.nvog.nl](http://www.nvog.nl)). Patients with overweight or obesity have additional risks during pregnancy compared to normal weight women. The risks involve: hypertension (OR: 2.2), preeclampsia (OR: 1.8-2.7), pregnancy-induced diabetes (OR: 2.2-3.4), caesarian section (OR: 1.3-2.4) (see tables of evidence in appendix). These risks are not influenced by fertility treatment. Lifestyle intervention aims to reduce the involved pregnancy risks.

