### **Primary Objective:**

Does a structured lifestyle program aiming at a weight reduction of 5%-10% reduce the need for fertility treatments due to an increase in spontaneous conception rate and treatment dependent or treatment independent life birth rate?

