#### 5.1.3 Secondary efficacy endpoints

Secondary outcome parameters are:

1. Pregnancy outcome and -complications: miscarriage, gestational diabetes, Pregnancy induced hypertension, preeclampsia, HELLP, prematurity < 37 weeks, macrosomia (> p90 (Large for Gestational Age), induction of labour, prolonged duration of labour, operative delivery, assisted delivery and increased blood loss, and multiple pregnancies
2. Percentage of women needing fertility treatment in both groups (OI, IUI, IVF, ICSI) and ongoing pregnancy rates in these treatments.

3. Quality and number of oocytes and embryos and cryo embryos resulting from an IVF or ICSI procedure and the amount of embryos per transfer and implantation rate of transferred embryos
4. Complications during fertility treatment: ovarian hyperstimulation syndrome, infection, tubal pregnancies, torsion (etc).
5. Perinatal outcome: stillbirth, pregnancy duration, body weight, Apgar scores, arterial pH, congenital anomalies and neonatal admission to a neonatal medium, high or intensive care unit.
6. Quality of life, pre-pregnancy body weight, weight gain during pregnancy, waist circumference, behaviour influencing weight, i.e. nutritional habits and exercise pattern, blood pressure, glucose/insulin ratio (HOMA), hormonal profile (androgens, adipokines and cytokines) and costs.

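### Spontaneous versus treatment-induced pregnancy is a post-randomisation outcome and cannot be a subgroup; rates by mode need competing-event handling and a stated caveat about the treatment delay

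*Supplement*

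**What the plan says.** The subgroup paragraph of SAP section 6.6 reads "Exploratory subgroup analyses of the primary outcome and ongoing pregnancy rates will be performed for spontaneous and treatment-induced pregnancies". It continues with BMI, ovulatory status, waist-hip ratio and age, and ends "based on tests of interaction with treatment group". Section 8.2 of the current protocol (version 5) has the same list for the primary outcome: "Exploratory subgroup analyses of the primary outcome will be performed for spontaneous and treatment-induced pregnancies".

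Just before that paragraph, SAP 6.6 describes the Kaplan-Meier, log-rank and Cox analyses and adds: "These analyses will also be performed for spontaneous and treatment-induced pregnancies separately". Censoring is defined only for women who stop or finish the study without becoming pregnant. Nothing is said about a woman who conceives by the other mode.

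Three other places bear on the point:
- The protocol's Primary Objective asks whether the programme will "reduce the need for fertility treatments due to an increase in spontaneous conception rate". The sentence goes on to name live birth, with or without treatment.
- The percentage of women needing fertility treatment is a secondary endpoint in SAP 5.1.3.
- The protocol Summary says that "fertility treatment in the intervention arm will be delayed for a maximum of 6 months". Protocol 6.3 (Start of fertility treatment) lets the wait end earlier, at the weight target or at a BMI below 29. Under protocol 5.1, usual-care women with an indication start without that wait, and those with a favourable prognosis are managed expectantly.

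**The concern.** BMI, ovulatory status, waist-hip ratio and age can be fixed at randomisation. Mode of conception cannot. It is known only once a woman conceives, and a woman who never conceives belongs to neither level. Yet both named outcomes, the primary outcome and the ongoing pregnancy rate, count non-conceivers as failures. No denominator within a level preserves the randomised comparison, and an interaction test between arm and mode has no causal reading.

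The time-to-event analyses by mode raise a second issue. A conception by one mode precludes a first conception by the other, so each is a competing event for the other. One minus Kaplan-Meier with the competing event censored estimates a probability that is too high.

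The third issue is interpretation. While treatment is withheld in the lifestyle arm, conceptions there are spontaneous by construction, whereas indicated women in usual care can already conceive on treatment. A lower treatment-induced rate and a higher spontaneous share can therefore appear with no change in fertility. Given the Primary Objective, that pattern could be reported as less need for treatment when treatment was only postponed.

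**Working it through.** The plan gives no figure for this analysis, so the check is an illustration.

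**Inputs from the documents.** Follow-up T = 24 months (protocol Summary). Delay D of up to 6 months (protocol Summary), ending earlier in some women (protocol 6.3). Usual-care rate 45% (SAP 6.1). Planned 285 women per arm (SAP 6.1).

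**Assumptions not in the documents.** The 45% is a birth rate and is used here as the 24-month conception rate. A share f of usual-care conceptions is spontaneous, with f from 20% to 50%. Hazards are constant, the programme has no effect on fertility, every usual-care woman has access to treatment from month 0, and every lifestyle woman from month D.

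**Model.** Total monthly hazard h = -ln(1 - 0.45)/24 = 0.02491; spontaneous hazard s = f × h. In usual care, spontaneous conception is 0.45f and treatment-induced conception is 0.45(1 - f). In the lifestyle arm:
- still not pregnant at D: S = exp(-sD)
- conception between D and 24 months among those women: F = 1 - exp(-h(24 - D))
- treatment-induced = S × F × (1 - f)
- spontaneous = (1 - S) + S × F × f

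**Worked case, f = 50%, D = 6.** s = 0.012455, S = 0.9280, F = 0.3613. Treatment-induced = 0.9280 × 0.3613 × 0.5 = 16.8%, against 22.5% in usual care (RR 0.75). Spontaneous = 7.2% + 16.8% = 24.0%, against 22.5% (RR 1.07). The spontaneous share of conceptions is 59% against 50%. Total conception falls from 45% to 40.7%.

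**Range.**

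| f | D (months) | RR treatment-induced | RR spontaneous | Spontaneous share, usual care → lifestyle |
|---|---|---|---|---|
| 20% | 6 | 0.78 | 1.11 | 20% → 26% |
| 35% | 6 | 0.76 | 1.09 | 35% → 43% |
| 50% | 6 | 0.75 | 1.07 | 50% → 59% |
| 20% | 3 | 0.89 | 1.06 | 20% → 23% |
| 35% | 3 | 0.88 | 1.05 | 35% → 39% |
| 50% | 3 | 0.87 | 1.03 | 50% → 54% |

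The result depends little on the 45%. With 60% conceiving instead, h = -ln(0.40)/24 = 0.03818, and the six-month RR for treatment-induced conception is 0.74 (f = 50%: 22.2% against 30%) to 0.79 (f = 20%: 38.0% against 48%).

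**Chance of a misleading test.** With 285 per arm and a simple two-sided 5% comparison of treatment-induced conception, the delay alone gives significance in about 41% to 53% of trials at six months and 13% to 16% at three months.

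**Percentage treated.** If a fraction q of women has an immediate indication (assumed 50% to 90%), the percentage ever treated is q in usual care and q × exp(-6s) in the lifestyle arm, because some conceive while waiting. The difference runs from 1.5 points (q = 50%, f = 20%: 50% to 48.5%) to 6.5 points (q = 90%, f = 50%: 90% to 83.5%).

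**Kaplan-Meier by mode.** If the other mode is censored, the usual-care estimate at 24 months for f = 50% is 1 - exp(-24 × 0.012455) = 1 - 0.55^0.5 = 25.8% for each mode, against a true 22.5%. The two add up to 51.7%, although only 45% conceive.

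**The case against.** The strongest reply concerns importance. The subgroup analysis is labelled exploratory and, like the analyses by mode, goes to a separate manuscript. SAP 5.1.2 pools both modes in the primary endpoint. A reader might infer that the primary comparison is compromised; the documents do not support that.

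A reader might also infer that the whole primary objective rests on mode of conception. It does not, because the same sentence names live birth, and treatment need has its own secondary endpoint. Nor is every use of mode faulty. SAP 6.6 tabulates "Mode of conception: spontaneous versus fertility treatment (OI, IUI, IVF/ICSI); number of fertility treatment cycles" over started participants, which is a legitimate comparison of two strategies with the delay as part of one of them.

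The six-month figures are close to an upper bound. Some women reach the weight target early, some usual-care women are managed expectantly and have no treatment to delay, and SAP 6.1 expects 20% drop-out from the intervention arm. It would also be too strong to say that the delay produces many more spontaneous conceptions: with f = 50% the rise is 1.5 points, and total conception falls visibly.

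Finally, censoring of the other mode is an inference, since the SAP is silent. If it is censored, cause-specific Cox models remain standard and only the Kaplan-Meier percentages are biased.

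All of this limits the weight and size of the point. It does not rescue the subgroup. Even if the interaction wording is read as applying only to the later factors in the list, mode of conception is still listed as a subgroup. Nor do the documents say that the delay shifts mode of conception and treatment use; they say only that there is no evidence of harm to pregnancy chances.

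**Conclusion.** The point holds in a limited form. Mode of conception cannot serve as a subgroup or interaction factor in SAP 6.6 or protocol 8.2. That conclusion is structural and needs no assumption. The rates by mode lack a rule for the competing event; if the other mode is censored, each is overstated by about 3 points in the equal-share illustration.

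The delay alone lowers treatment-induced conception, with an RR of about 0.75 to 0.78 for a full six months and 0.87 to 0.89 for three, and it raises the spontaneous share. These figures assume constant hazards, 45% conceiving in usual care, 20% to 50% of them spontaneously, and immediate access to treatment in usual care. The true shift is smaller where women are managed expectantly. The pooled primary analysis and the sample size are unaffected. The change should be made, but it concerns exploratory and secondary results and how they are read.

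**What to change.** 1. Remove spontaneous versus treatment-induced pregnancy from the subgroup and interaction list in SAP 6.6 and protocol 8.2.
2. Report spontaneous and treatment-induced conception as competing outcomes, by cumulative incidence per arm with all randomised women as denominator. Cause-specific Cox models may stay, with the handling of the other mode stated.
3. State in SAP 5.1.3 and 6.6 that 24-month differences in mode of conception and in the percentage treated include the protocol-imposed delay, and cannot alone be read as reduced need for treatment.

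Two substitutes may look attractive but are not recommended. Treatment use per month of access conditions on when access begins, which in the lifestyle arm depends on weight loss after randomisation. A comparison limited to couples with an expectant-management prognosis is not free of the delay either, because a couple close to three years of subfertility can become due for treatment within the first six months.

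The cost is SAP and protocol wording and minor analysis code. No new data are needed.
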